### Adverse Events and Dropouts

All adverse events, deaths, dropouts, or withdrawals from the study will be recorded and documented. If the patients no longer want to participate in the study, they can withdraw their consent at any time without having to give a reason. After withdrawing they will be given standard care treatment. The patient’s reason for withdrawal, if any is given, will be documented. In this case, the project team will collect the equipment upon request. Patients who do not participate actively in the intervention will still be included in the study and analyzed according to the intention-to-treat approach. These patients will be allowed to use the project equipment as long as they want. Technical problems with the equipment will be recorded and documented.

### Statistical Analysis

The applied statistical methods will be used to investigate differences between patients in the intervention group and the control group. Statistical analyses will be used to explore the normal distribution of the sample, the SD, the hypothesis tests, and the *P* values. Nevertheless, a 2-tailed *t* test between the intervention and control groups will be performed in order to compare baseline data between the 2 groups, and a 2-way ANOVA with repeated measures will also be performed to compare the 2 groups in relation to their outcomes. All the statistical analyses will be performed using SPSS Statistics (version 25; IBM Corp). Data will be analyzed for gender differences in both primary and secondary outcomes. If there is any missing data, it will be analyzed based on the data received from the questionnaires. If there is too much data missing, a sensitivity test will be performed based on the demographic data.

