## Abstract

**Background:**

The World Health Organization defines end-of-life palliative care as “prevention and relief of suffering, by means of early identification and impeccable assessment and treatment of pain and other problems, physical, psychosocial and spiritual.” Over 20 million people worldwide are in need of palliative care. In Denmark, palliative care is given at a general and a specialist level. The general level comprises health care professionals (HCPs) who do not perform palliative care full-time. The specialist level comprises specialized palliative care (SPC), where HCPs perform palliative care full-time. In total, 20%-30% of patients who need palliative care are referred to SPC. Challenges with SPC include a short time span from referral to end of life, patients who are very ill and may therefore find it hard to travel to an outpatient clinic, and the SPC unit having a relatively small staff. The need for SPC is expected to rise, as the number of patients dying from terminal diseases is increasing. Telehealth has been successfully implemented in different home care settings, including palliative care.

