## Introduction

The World Health Organization defines end-of-life palliative care as “prevention and relief of suffering, by means of early identification and impeccable assessment and treatment of pain and other problems, physical, psychosocial and spiritual” [1]. The aim of palliative care is to provide relief from pain and other distressing symptoms offered by health care professionals (HCPs) at a general or specialist level, with a focus on addressing the needs of patients and their families [1,2]. More than 20 million people worldwide are estimated to be in need of end-of-life palliative care, equivalent to 377 adults in a population of 100,000, the majority of these being adults aged 60 years and older [2].

In Denmark, as in most other Western European countries, palliative care is provided at 2 different levels, a general and a specialist. The general level comprises HCPs, such as general practitioners (GPs) and primary care nurses, who do not perform palliative care on a full-time basis. The specialist level comprises specialized palliative care (SPC), where HCPs perform palliative care on a full-time basis at a specialist level [3]. It is expected that the basic level palliative care can address around 70%-80% of the patients in need of palliative care. The remaining 20%-30% of patients, having more complex problems, need SPC. SPC consists of specialized palliative care teams (SPCTs) placed at large hospitals serving a wider geographical area with home visits and cross-sector communication with patients, relatives, and other HCPs capable of caring for the patients.

Among patients receiving SPC, more than 90% are diagnosed with cancer [4], with the remaining cases divided among patients diagnosed with terminal cardiac insufficiency, terminal chronic obstructive pulmonary disease, and terminal neurological disorders [2,4].

There are several challenges associated with SPC, such as the very short time span from referral to the end of the patient’s life [4] and the fact that patients are very ill and may therefore find it hard to travel to an outpatient clinic and that SPC unit often has a relatively small staff [2,5-7]. The need for SPC is expected to rise in the future, as the number of patients dying from life-threatening diseases, including cancer, is increasing [5,8]. As an increasing number of these patients prefer to be cared for at home, the demand for SPC is expected to increase [5,8].

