### Ethical Considerations

This study was approved by the ethical committee in Northern Jutland (N-202000094) and registered at ClinicalTrials.gov (NCT04995848). This study will be conducted according to the Declaration of Helsinki. Patients in palliative care and their relatives are a vulnerable group and will be informed thoroughly about the purpose of the study. Accordingly, it is specified that the patient can withdraw their consent at any given time in the study without having any consequences for their treatment. Individuals will be considered as participants in the trial, whereas their relatives will not be considered as participants. However, they are invited to voluntarily participate in the use of the digital platform TelePal. To clarify and ensure that all relatives are fully informed about the study and feel safe about their participation, a written letter of information was sent to all relatives. Patients are enrolled in the study for a maximum of 6 months or until (1) they stop being followed by the palliative team due to lack of symptoms or (2) they are diagnosed with delirium based upon the Confusion Assessment Method score [22,23]. Patients who develop cognitive impairment will be dismissed from the study, and patients who develop delirium will also be dismissed, and data collection will end immediately.

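### The planned repeated-measures ANOVA drops every patient with a gap in the analysed weeks, so the primary comparison would rest on a reduced group selected after randomisation

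*Protocol article*

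**What the plan says.** All references are to the protocol article.

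- **Method.** Statistical Analysis plans t tests for baseline data and, for outcomes, "a 2-way ANOVA with repeated measures will also be performed to compare the 2 groups in relation to their outcomes". The software is fixed too: "All the statistical analyses will be performed using SPSS Statistics (version 25; IBM Corp").
- **Schedule.** Table 1 has quality of life, the primary outcome, scored once a week in both arms and sense of security twice a week. Ethical Considerations sets the duration: "Patients are enrolled in the study for a maximum of 6 months or until" discharge from the palliative team for lack of symptoms, or delirium. That allows up to about 26 quality-of-life scores and about 52 security scores per patient.
- **Exits.** The same section dismisses patients who develop cognitive impairment, and "patients who develop delirium will also be dismissed, and data collection will end immediately". The Introduction notes "the very short time span from referral to the end of the patient’s life". Adverse Events and Dropouts provides for recording deaths, dropouts and withdrawals.
- **Analysis set.** Adverse Events and Dropouts states: "Patients who do not participate actively in the intervention will still be included in the study and analyzed according to the intention-to-treat approach".
- **Missing data.** Statistical Analysis says that analysis will use whatever questionnaire data were received, and adds: "If there is too much data missing, a sensitivity test will be performed based on the demographic data".

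**The concern.** Classical repeated-measures ANOVA, as run by the SPSS general linear model procedure, takes one row per patient with a column per occasion and deletes the whole row if any column is empty. In this population gaps will be common, and their causes are tied to the outcome. The sickest patients leave through death or delirium, some of the least symptomatic through discharge, and others miss forms when they feel worst.

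The patients kept are alive, lucid, still followed and fully compliant throughout the analysed weeks. That status is determined after randomisation and may be reached differently in the two arms, so the comparison no longer has the protection of randomisation, and it uses fewer patients than planned.

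Neither missing-data rule helps. Using the data received is not possible for a partial row in this method. A sensitivity test on demographic data has no stated trigger, and age or sex cannot show what quality of life was lost to decline or death.

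**Working it through.** **Starting number.** Sample Size states 91 per arm, from means 59.5 and 68.43 (difference 8.93), SD 20.5, 80% power and a 95% CI. The usual two-sided formula gives 2 × [20.5 × (1.960 + 0.842) / 8.93]² = 82.7, so 83 rather than 91. That mismatch is a separate matter. I use 91 as stated.

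**Complete rows.** The article gives no exit rate, completion rate or window, so the following are assumptions:

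- median time to any exit of 3 months = 3 × 4.345 = 13.04 weeks, at a constant rate;
- 5% of weekly forms missed while in the study, independently;
- baseline always present.

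Complete rows per arm over *k* follow-up weeks = 91 × 0.5^(k/13.04) × 0.95^k.

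| Window | Still in study | No missed form | Complete of 91 |
|---|---|---|---|
| Baseline + 4 weeks | 0.808 | 0.815 | 59.9 |
| Baseline + 12 weeks | 0.528 | 0.540 | 26.0 |
| 26 weeks | 0.251 | 0.264 | 6.0 |

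**Range over 26 weeks.** Here *S* is the share still in the study at week 26 and *c* the weekly completion probability. Complete rows = 91 × S × c^26. Power is for a two-sided t test on a single score at d = 8.93/20.5 = 0.436; with all 91 per arm it is 83%.

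| S | c | Complete of 91 | Power |
|---|---|---|---|
| 0.8 | 1.00 | 73 | 74% |
| 0.8 | 0.98 | 43 | 51% |
| 0.5 | 1.00 | 45 | 54% |
| 0.5 | 0.98 | 27 | 35% |
| 0.5 | 0.95 | 12 | 18% |

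A test that averages weeks would have somewhat more power per patient kept.

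**Effect of deletion alone.** To isolate it, hold the contrast fixed: week 4, adjusted for baseline, with an assumed within-patient correlation of 0.6 and exit unrelated to the score. The residual SD is 20.5 × √(1 − 0.36) = 16.4.

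| Patients used | Per arm | Power |
|---|---|---|
| All with a week-4 score (91 × 0.808 × 0.95) | 70 | 89% |
| Complete over weeks 1–4 | 60 | 84% |
| Complete over weeks 1–12 | 26 | 49% |

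Deletion costs little power over a short window and a great deal over a long one. These figures say nothing about bias, because exit was taken as unrelated to the score.

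**The case against.** Several points on the other side stand.

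1. **The window is not stated.** Weekly scoring and a 6-month maximum do not establish that all 26 occasions enter the ANOVA, and an analysis plan that is not shown may set a shorter window. So a reader should not conclude that only a handful of patients per arm will be analysed. What remains is that deletion applies to whatever window is chosen; on the assumptions above, even 4 weeks loses about a third.

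2. **Intention to treat is not flatly contradicted.** It is tempting to read the ANOVA as breaking a stated intention-to-treat analysis. The sentence concerns patients who are inactive in the intervention, and one who never uses the platform but returns every form is kept. The conflict is direct only for inactive patients who also miss forms. For everyone else it is a tension of principle.

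3. **The retained group is not simply the survivors.** Patients discharged for lack of symptoms are lost as well, so the direction of any bias cannot be settled from the article.

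4. **A large power gap should not be blamed on deletion alone.** Comparing an unadjusted complete-case average with an adjusted early analysis changes three things at once. With correlation 0.6, the same 26 complete patients per arm have about 43% power for the unadjusted mean of 13 occasions and about 84% for the baseline-adjusted mean of weeks 1–12 (exit unrelated to score). Complete cases over weeks 1–4, adjusted, reach about 98%. Averaging in the baseline, where no effect exists, also shrinks 8.93 to 8.93 × 12/13 = 8.24 without any selection.

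The reply that details belong in the analysis plan does not remove the point. The article does not leave method and fallback open; it names both, and the two do not suit these data.

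**Conclusion.** The concern holds as a mismatch between the named method, the missing-data rules and the way patients leave this trial. Followed as written, the plan gives a primary comparison on a reduced group selected after randomisation, and nothing in the article recovers the discarded scores or tests the effect of losing them.

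That conclusion rests on the stated method, schedule and exit rules. The size does not: about 60, 26 or 6 of 91 per arm follows from an assumed 3-month median exit, 5% weekly gaps and windows of 4, 12 or 26 weeks. Better retention or a shorter window would shrink the loss. The documents support neither a fixed power figure nor a direction of bias.

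It should be corrected before analysis, because the primary result depends on it.

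**What to change.** - **Model.** Replace the ANOVA with a linear mixed model (SPSS MIXED) on all available weekly scores of every randomised patient, with arm, week as a category, arm-by-week, baseline score and a within-patient covariance. Report by arm how many patients have no follow-up score.
- **Primary contrast.** Name one early contrast in advance, for example the arm difference at week 4 (when the EQ-5D is already scheduled) or the mean over weeks 1–4. An early contrast limits how much rests on patients who have died or left.
- **Interpretation.** Describe the result as a comparison while alive and in the study, and report deaths and each kind of exit by arm.
- **Sensitivity analysis.** Replace the demographic rule with an analysis that addresses outcome-related loss, for example one ranking death or exit for deterioration as the worst result. Run it regardless of how much is missing.

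**Cost.** A change of wording and a little more analysis work, in the same software and with no extra data. The estimate then depends on a missing-at-random assumption, which the data cannot confirm; that is why the sensitivity analysis is needed.

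### The stated sensitivity analysis for missing quality-of-life data has an undefined trigger and rests on demographics, although patients leave this trial mainly because of their health

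*Protocol article*

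**What the plan says.** The Statistical Analysis section of the protocol article has two sentences on missing data. The first is "If there is any missing data, it will be analyzed based on the data received from the questionnaires". The second is "If there is too much data missing, a sensitivity test will be performed based on the demographic data". No amount is given for the trigger, and the article states no other sensitivity analysis. The outcome analysis is described as "a 2-way ANOVA with repeated measures will also be performed to compare the 2 groups in relation to their outcomes".

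The routes out of follow-up are set elsewhere. Under Ethical Considerations, participation lasts at most 6 months or ends when "they stop being followed by the palliative team due to lack of symptoms". Cognitive impairment also ends it, and "patients who develop delirium will also be dismissed, and data collection will end immediately". The Introduction names "the very short time span from referral to the end of the patient’s life" as a known difficulty of this setting.

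Under Adverse Events and Dropouts, "All adverse events, deaths, dropouts, or withdrawals from the study will be recorded and documented". For withdrawals the entry is conditional: "The patient’s reason for withdrawal, if any is given, will be documented". Table 1 has QoL, the primary outcome, measured once weekly in both groups.

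**The concern.** A sensitivity analysis for missing data should test the assumption most likely to fail. Here that is the assumption that patients who stop answering resemble those who continue. Discharge for lack of symptoms removes patients who are doing well. Delirium, cognitive impairment and death remove patients who are doing badly. Both routes run through current health, and age, sex and similar variables are likely to track that only loosely. The two arms could therefore look alike demographically among completers while having lost quite different patients.

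The trigger has a separate weakness. The volume of missing data does not show whether a comparison is biased. A large loss of the same kind in both arms may do little harm to the difference, whereas a moderate loss that follows health in one arm only can create a difference from nothing. A rule that opens the check only past an unspecified volume can leave it closed when it is needed.

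At stake is whether a reader can tell a true QoL effect from a difference in who remained to answer.

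**Working it through.** **Inputs from the article.** SD 20.5 and means 59.5 and 68.43 (Sample Size), so the planned difference is 68.43 − 59.5 = 8.93 points. There are 91 patients per group, and QoL is scored weekly.

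**Inputs not in the article, so assumed.** The share missing, and how strongly exit depends on QoL. No dropout or death rate is given.

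**Step 1: bias in one arm's mean.** Let z = (QoL − mean)/SD and logit P(missing) = −1 − b·z, so that worse QoL makes a missing score more likely. The observed mean is then too high by 20.5 × E[z(1 − P)] / E[1 − P].

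| Slope b | Share missing | One-arm bias (points) |
|---|---|---|
| 1.0 | 30.3% | 5.24 |
| 0.8 | 29.3% | 4.28 |
| 0.5 | 27.9% | 2.73 |
| 0 | 26.9% | 0 |

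**Step 2: bias in the comparison, with no true effect.** Only the difference between arms matters.

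- 1.0 in both arms: 5.24 − 5.24 = 0
- 1.0 vs 0.8: 5.24 − 4.28 = 0.96, about 1.0
- 1.0 vs 0.5: 5.24 − 2.73 = 2.51, about 2.5
- 1.0 vs 0: 5.24 − 0 = 5.24, about 5.2

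**Step 3: would the amount missing give warning?** In the last case the arms lose 0.303 × 91 = 27.6 and 0.269 × 91 = 24.5 patients, a gap of about three. In the first case the rates are identical and the comparison is unbiased. Similar amounts missing are thus compatible with a false difference of 0 or of 5.2 points.

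**Step 4: what adjustment recovers.** Regressing QoL on an auxiliary variable among those observed and predicting for everyone, in the b = 1.0 arm:

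| Auxiliary information | Bias left | Removed |
|---|---|---|
| None | 5.2 | – |
| Demographics, R² = 0.05 | 5.0 | about 4% |
| Demographics, R² = 0.10 | 4.8 | about 9% |
| One earlier weekly score, r = 0.6 | 3.5 | about one third |

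The earlier score also leaves most of the bias, which is why imputation has to be followed by a shift analysis.

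**Step 5: exits in the other direction.** If a quarter of exits follow the reverse slope, as discharge for lack of symptoms would, the one-arm bias falls from 5.2 to 2.6. At half it is about 0.

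**Step 6: a check at the trial's size.** A second simulation used 91 per arm, eight weekly follow-up scores, no true effect, and exit depending on the last score in the control arm only (59% vs 73% completers). The complete-case difference was −5.66 points, or −5.64 after adjusting for age and sex. An age comparison of completers and non-completers was significant in about 6% of runs, which is chance level. A baseline-QoL comparison was significant in 54%. In this model age explains very little of QoL by construction, so the R² of 5 to 10% in Step 4 is the more generous case for demographics.

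**The case against.** The strongest reply is that the text is condensed and open to a kinder reading. The sentence before the quoted one says that missing data will be handled from the questionnaires received, and weekly scores are questionnaires received. The outcome analysis is also repeated-measures. A reader might infer that the plan ignores earlier scores altogether; the article does not support that. What it does show is that the stated sensitivity test names demographics and nothing else.

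Other strong readings also go too far:

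- **That no other sensitivity analysis exists.** The SAP and full protocol are not shown, and a numerical threshold or an imputation model may sit there. The point concerns the trigger and basis that the article does fix.
- **That a demographic test can detect nothing.** It picks up whatever part demographics predict.
- **That exit reasons are available for everyone.** Withdrawal reasons are documented only if the patient offers one.
- **That unblinded staff would judge the trigger.** Details on the RCT says that one person was blinded and does not say in which role; it could be the analyst.
- **That 5.2 of the planned 8.93 points would be spurious.** The 5.2 becomes a bias in the comparison only if health-related exit occurs in one arm alone. With equal mechanisms it is 0, and exits for improvement offset exits for worsening.

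These limits stand, and they narrow the point. They do not rescue the rule, since a sensitivity analysis exists to show which of these situations occurred.

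**Conclusion.** The point holds in limited form. The article commits to a check whose trigger is undefined and whose basis fits poorly with exits that its own rules and setting tie to health. Under the assumptions shown (SD 20.5, about 30% missing, no true effect), the false between-arm difference ranges from 0 to about 5.2 points, with 1.0 and 2.5 for intermediate contrasts. A demographic adjustment would remove roughly a tenth of it at best. The documents do not allow the actual size or direction to be derived, and they do not show that the result will be biased. The weakness is that the stated check could not separate the harmless cases from the harmful ones. It should be corrected before analysis.

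**What to change.** Replace the quoted sentence with a sensitivity analysis of the primary outcome that is run whatever the amount missing:

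1. Tabulate exits by arm, week and reason where recorded, with a category for reason not given.
2. Impute the missing scores of living patients from earlier weekly QoL scores, arm and demographics.
3. Shift the imputed values separately by arm over a range that includes no shift and reaches about the planned difference, for example 0 to 9 points in each direction. Report the shift at which the conclusion changes.
4. Report deaths by arm beside the QoL result, do not impute scores after death, and state that the QoL comparison is among patients alive.

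The cost is a change of wording and some extra analysis. The conclusion may also turn out less firm. No new data collection is needed, because the weekly scores are already planned and deaths, dropouts and withdrawals are already recorded.

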### Qualitative Analysis

All interviews will be transcribed into Word (Microsoft Corp) files. The data will be coded in NVivo (version 12.0; QSR International) inspired by methods developed by Brinkmann and Kvale [33]. Two researchers ([name] and BD) will conduct the interviews and analysis of the data. The data will be presented in themes, findings, and with citations.

